## Abstract

**Background:**

Nursing home residents are typically older adults with high levels of chronic illness and impairment. As such, they are particularly susceptible to severe complications and mortality from COVID-19. Since all nursing home residents are at increased risk, nursing home care staff need to know what residents would want to happen should they become infected with COVID-19. This study aims to develop and evaluate advance care planning (ACP) COVID-centric online training and information resources for nursing home staff and family members of residents, to improve care at the end of life during a COVID-19 outbreak. Based on the findings we will develop implementation guidelines for nursing homes to ensure wider impact and application during the pandemic and beyond.

**Methods:**

The content of the training and information resources will be based on a rapid review of literature and guidance on ACP in the context of COVID-19 and consultation with the study expert reference group. An integrated communications company will then work alongside the research team to design the online training and information resources. To evaluate the resources, we will employ a multiple case study design where a nursing home (defined as an institutional setting in which nursing care is provided to older adults on-site 24 h a day) will be the unit of analysis or ‘case’. The RE-AIM (reach, effectiveness, adoption, implementation, maintenance) framework will guide the evaluation of implementation of the training and information resources. We will recruit and interview staff and family members from between 6 and 9 nursing homes across Northern Ireland, England and Scotland and gather quantitative data from a feedback survey included in the training and information resources.

**Discussion:**

The Necessary Discussions study is very timely given the challenging experiences of nursing homes, their staff, residents and their family members during the COVID-19 pandemic. It meets a key need and addresses an important gap in research and practice. The training and information resources will be ‘COVID-centric’, but they will also have a longstanding relevance for future ACP practice in UK care homes.

**Trial registration:**

ISRCTN registry (ID 18003630) on 19.05.21

## Background

Nursing home residents are typically older adults with high levels of chronic illness and impairment. As such, they are particularly susceptible to severe complications and mortality from COVID-19 [1]. Since all nursing home residents are at substantial risk, nursing home staff need to know what residents would want to happen should they become infected with COVID-19. One way of ensuring that care reflects the wishes and preferences of residents, is to develop an advance care plan. Although it is regarded as good practice for advance care plans to be in place at the earliest possible opportunity upon admission to a nursing home, the COVID-19 pandemic and the sudden manner of illness and rapid deterioration of nursing home residents, and in some cases death, has amplified the need for documented advance care plans [2, 3].

Through a consensus study, Sudore and colleagues provide the following definition: “Advance care planning is a process that supports adults at any age or stage of health in understanding and sharing their personal values, life goals, and preferences regarding future medical care. The goal of advance care planning (henceforth referred to as ACP) is to help ensure that people receive medical care that is consistent with their values, goals and preferences during serious and chronic illness. or many people, this process may include choosing and preparing another trusted person or persons to make medical decisions in the event the person can no longer make his or her own decisions.” [4]. More broadly, ACP is viewed as an on-going conversation which should involve the provision of information [5] to patients’ / residents’ and family members’ “… as a means of navigating the uncertainties at the end of life by identifying and supporting patients’ needs and preferences for care.” [6].

It is good practice for ACP to have several documented outcomes, including clarification of patient’s preferences, values and aims for future medical treatments and care; the identification of the refusal of specific future treatments should the patient or resident later become unable to communicate; and the appointment of a person to take decisions on the patient’s behalf if they subsequently lose decisional capacity [6, 7].

ACP conversations and processes are regarded as difficult and often complex for both nursing home staff and family members [3–6]. However, given the emergence of COVID-19 as a global pandemic, as classified by the World Health Organisation on the 11th March 2020, ACP practice and its potential for ensuring high quality person-centred care at the end of life, has arguably become more important than ever. It is vitally important that both nursing home staff and family members feel competent and confident to engage in ACP conversations. The provision of training and information resources are means of empowering these groups to have these difficult but ‘necessary discussions’. However, critical gaps have been highlighted in research, policy and practice around ACP tools, training and information resources, which are exacerbated within the context of COVID-19.

In a broader nursing home context, the effectiveness of staff training [8] and quality and accessibility of information resources for family members [9–11] have both been frequently cited as being underdeveloped fields of research and practice. Furthermore, with respect to COVID-19, a recent review published by The Centre for Evidence Based Medicine at the University of Oxford on ACP in the community [3] found that 1) there often exists a lack of awareness among key stakeholders about ACP; 2) there is a need to develop information and training resources – particularly online – to support ACP practice; 3) there is a paucity of research on ACP in a COVID-19 context.

The aim of the ‘Necessary Discussions’ study is to address these aforementioned gaps and develop and evaluate ACP COVID-centric online training and information resources, alongside implementation guidelines for nursing homes to improve care at the end of life during a COVID-19 outbreak. Moreover, the study will:
Develop an online ACP COVID-centric training resource (a website) for nursing home staff including conversational prompts to aid conversations.Prepare an online ACP COVID-centric information resource for family members.Evaluate the training and information resources and identify the facilitators and barriers to implementing these resources in a nursing home context.Produce implementation guidelines for online ACP COVID-centric resources that will facilitate widespread use within UK nursing homes.Identify strategic partnerships that will facilitate the integration of the ACP online resources into nursing home practice.

## Methods/design

### Design

The study will employ a multiple mixed methods case study design where a nursing home will be the unit of analysis or ‘case’ [12]. Case study is an approach that is widely adopted in nursing and care home research [13], as well as related areas such as palliative care [14, 15]. Central to a case study approach is to triangulate multiple methods and sources of evidence to explore phenomena that is both complex and context-dependant (Yin, 2009). A prospective case study design will allow us to understand the implementation process, and barriers and facilitators for the educational and information resources. The RE-AIM (reach, effectiveness, adoption, implementation, maintenance) framework will guide the evaluation of the educational and information resources [16]. There are four key phases to the study:
Establishment of an Expert Reference Group (ERG) and International Observer Panel (IOP)Rapid review of ACP resourcesDevelopment of the educational and information resources (website)Evaluation of the ACP training and information resources and development of the implementation guidance

### Phase 1

#### Establishment of an expert reference group and international observer panel

The Expert Reference Group (ERG) will include up to 14 individuals. The group will include representation from nursing home managers, nursing home direct care providers, public involvement representation including family members, knowledge expert on ACP, third sector organizations (e.g., Age UK, Marie Curie, Dementia UK), and a healthcare provider with COVID-19 care experience. The ERG will provide advice on all appropriate aspects of the project, review project progress and outputs, adherence to the protocol, and act as a network based on the project objectives concerning dissemination. The ERG will meet as a group to discuss intervention development at three milestone points: 1) at the project launch; 2) completion of the content for the ACP online resources; 3) reviewing evaluation results. Outside of these meetings ERG members will be consulted on an individual basis on study matters where necessary. All communication will be conducted on MS Teams (GDPR compliant) or via telephone.

Recognising COVID-19 as a global pandemic, an international observer panel (IOP) of experts in palliative, nursing home care will be established. Drawn from Italy, Czech Republic, Netherlands, Republic of Ireland and Canada this panel will monitor project activities with the view of applying outputs in their home countries and for wider dissemination purposes.

### Phase 2

#### Rapid review of ACP resources

A review of currently available UK ACP resources that focus on COVID-19 will be conducted. ACP resources will be included from government and professional association websites and personal communications. We will use ACP resources that are known to the research team, put a ‘call out’ on social media platforms and run guideline specific searches on the Turning Research into Practice (TRIP) database and Google. A review and synthesis of relevant material will contribute to the development of the online ACP COVID- centric training resource for nursing home staff and family members by identifying existing content, gaps in current resources specific to a UK context.

### Phase 3

#### Development of online training and information resources

Staff training and information resources for family members will be developed using findings from phase 2. An integrated communications company will be commissioned to develop a website to present the resources for each group. The company specialise in digital resources and have worked with a vast range of public and private sector clients.

It is anticipated that the following content will be developed: expert interviews giving guidance on topics and communication tips; interviews with staff about real life experiences, enabling peer to peer learning; resource planning tips, including handling technology; infographics highlighting key messages and practical techniques. It is anticipated that the training resource for nursing home staff will cover the following themes: an introduction to advance care planning, including benefits and misconceptions; advance care planning in the context of COVID-19, including emergency care planning; how to complete an advance care plan during COVID-19, including hosting a family meeting online; recording and sharing advance care plans during COVID-19, including identifying stakeholders; tips and guidance for having advance care planning conversations; self-care during COVID-19. Communication tips will be embedded in each theme. Due to infection control protocols during a COVID-19 outbreak conversation prompts for ACP conversations will be developed in anticipation that nursing staff communication with family members will frequently be via telephone or video only. It is anticipated that the online ACP information resource for family members will include information on key terms used in ACP; review of ACP, its purpose, contents who is involved and ways to take part in ACP conversations during COVID-19.

The research team and ERG will review and provide feedback on the training and information resources prior to developing the online platform. The language used will be simple and informative to ensure it is user friendly. Future considerations will include the use of subtitles that will allow for inclusiveness of those with sight or hearing impairments and people who do not speak English.

### Phase 4

#### Evaluation of the ACP online intervention

The study will employ a case study approach where a nursing home will be the unit of analysis or ‘case’. Participants at each nursing home (care staff and family members) will be asked to complete the training (the intervention) and provide feedback (the evaluation). A prospective case study design will allow us to understand the implementation process for the intervention (1, 2). The team have established relationships with many nursing home providers who have indicated their willingness to participate in what they see as vital research. The NIHR initiative Enabling Research in Care Homes (ENRICH) network will also be engaged, if needed, in recruiting nursing homes.

The RE-AIM framework will guide the evaluation [16]. A major feature of RE-AIM is that it shifts the focus from randomized efficacy trials to longer-term effectiveness in a real- world setting. The dimensions of the framework are as follows:
Reach, the proportion and representativeness of identified nursing home staff, family members and residents who access the online training resource and review resource featuresEffectiveness, the impact the ACP online intervention has on staff and family members knowledge and attitudes towards the intervention (content, aesthetic properties, usability) and ACPAdoption, assess nursing home staff and family member acceptability of the trainingImplementation, assessment of the fidelity of implementing the protocolMaintenance, determine whether nursing home managers and staff wish to continue the intervention

#### Settings, participants and data collection

Sampling will occur at three levels in this project: (1) across geographic locations; (2) selection of multiple quantitative and qualitative data sources within each nursing home; and (3) ensuring a spread of staff and family member characteristics. The study aims to recruit up to 9 nursing homes across Northern Ireland (*n* = 3), Scotland (*n =* 3) and England (*n =* 3). We aim to recruit within each site (and in total) (Table 1):
1 nursing home manager (*n =* 9)4 nursing home staff per site (*n =* approximately 36)6 family members relating to 6 residents (*n =* approximately 54)

**Table Tab1:** **Table 1** Phases, data collection, methods and themes

Phase	Data collection methods and themes
**1. Environmental Scan**	**Interviews with nursing home manager** ***(n = 1)*** **Key themes:** Current practice; Impressions of the proposed COVID; ACP intervention; Potential barriers and facilitators towards implementation. **Nursing home profile questionnaire** ***(administered as part of interview with nursing home manager)*** **Key themes:** Resident and facility profile (including COVID outbreaks); Care home policies and procedures; Staff profile; Staff training; Use of technology; Contact with health and social care professionals; Response to COVID-19. **Interviews with nursing homes staff** ***(n = up to 4 registered nurses who undertake training)*** **Key themes:** Demographics**;** Current practice; Experience (including confidence & concerns about completing ACP in the context of COVID-19); Communication & technology; The role of family members; Impressions of the COVID-19 online training; Potential barriers & facilitators. **Interviews with family carers** ***(up to n = 6)*** **Key themes:** Background information/Demographics; Use of technology and current communication approach with nursing home/relative; Information needs
**3. Follow up data collection** Completed 1–2 weeks following delivery of the online training by participants recruited during the environmental scan	**Interviews with nursing home managers, staff, family carers & the external facilitator** ***(n = see above)*** **Key themes. Family carers:** Satisfaction; Acceptability; Impact on attitudes; knowledge & behaviour; Technology & communication**. Nursing home manager/staff**: Satisfaction; Acceptability; Impact on attitudes, knowledge & behaviour; Communication & technology; Implementation. **External facilitator**: Satisfaction; Acceptability; Training & sustainability. **Feedback questionnaires** (including website user experience, preparedness, communication)

##### Timepoint 1

Data will be collected at two time points. Firstly, environmental scan interviews will be conducted with nursing home managers, staff and family members in each participating home. The aim of the environmental scan is to provide a facility profile describing the relevant characteristics of the nursing home, current practice and to identify potential barriers and facilitators for accessing and implementing learning. A nursing home profile questionnaire will be administered to nursing home managers. The environmental scan provides valuable context for the case study analysis.

Interviews will take approximately 30–60 min. Once the first interview is complete, participants will be emailed details on how to access the training and information resources (website). After care staff and family members have accessed and navigated to the end of the online resources, they will be required to complete an automated online evaluation questionnaire.

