##### Time point 2: 1–2 weeks post intervention

A follow up interview with all participants in timepoint 1 will be conducted 1–2 weeks after participants have accessed the training or information resources. All interviews will be conducted by telephone or on MS Teams. Interviews will take approximately 30–60 min.

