### Data management and analysis

Within each nursing home, data will be analysed 1) within data set (nursing home), followed by a 2) cross-case analysis. The analysis will be guided by the RE-AIM framework [16]. Reach will be assessed by website analytics (numbers of visits, time spent on site/sections; pathway through website). The domains; Effectiveness, Adoption, Implementation, and Maintenance, will be assessed through quantitative descriptive indicators and qualitative interviews with both nursing home staff and family members.

Interviews will be digitally recorded and transcribed verbatim. We will analyse qualitative data in NVIVO and follow the framework analysis style outlined by Ritchie and Spencer [20]. Descriptive statistics will be used to analyse the quantitative data. Syntheses across quantitative and qualitative data will occur at the interpretation stage creating a single nursing home case study. The nursing home case study will be summarized in a logic model. Following individual nursing home case study analysis, a cross case synthesis will be performed across all case study sites. Following the evaluation and ERG consultation, the online training and information resources will be refined and implementation guidelines developed.

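### The end-of-website questionnaire describes finishers only, and participants who never open the site have no follow-up interview date

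*Protocol article*

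**What the plan says.** Staff and family members are enrolled and interviewed first. Access details are emailed only after that interview (Timepoint 1).

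**Questionnaire.** Timepoint 1 then states: "After care staff and family members have accessed and navigated to the end of the online resources, they will be required to complete". The form meant here is the evaluation questionnaire, which is online and opens automatically. The Methods part of the abstract likewise describes the quantitative feedback survey as built into the resources. Table 1 says that it covers user experience of the website, preparedness and communication.

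**Follow-up interview.** The Time point 2 section states: "A follow up interview with all participants in timepoint 1 will be conducted 1–2 weeks after participants have accessed the training or information resources". Row 3 of Table 1, follow-up data collection, is headed: "Completed 1–2 weeks following delivery of the online training by participants recruited during the environmental scan". That row lists both the interviews and the feedback questionnaires.

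**Use of the data.** Under Data management and analysis, Reach comes from website analytics. Effectiveness, Adoption, Implementation and Maintenance "will be assessed through quantitative descriptive indicators and qualitative interviews with both nursing home staff and family members". The section on evaluation of the online intervention defines Adoption as acceptability. One stated aim in the Background is: "Evaluate the training and information resources and identify the facilitators and barriers to implementing these resources in a nursing home context".

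**The concern.** A questionnaire that opens only at the last page selects its respondents on an outcome of the intervention. Someone who finds the site hard to use, too long or irrelevant, and leaves, never sees the form that asks about usability. The numerical feedback is then a description of people for whom the resource worked well enough to finish.

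The interview could fill that gap, but its clock starts at access. A participant who never logs on has no starting point, so the promise to interview everyone cannot be carried out as written for that person. Yet such participants can say most directly why the resource was not taken up, and barriers to implementation are a stated aim. The findings also feed the refinement of the resources and the implementation guidelines.

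Separately, a rating given on leaving the site and a rating given one to two weeks later are different measurements. The article should state one of them.

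**Working it through.** **Step 1. What each group provides after access is offered, as written.**

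| Group | Questionnaire | Follow-up interview | Analytics (Reach) |
|---|---|---|---|
| Opened and finished | Yes | Yes, 1–2 weeks after access | Yes |
| Opened, stopped part-way | No route stated | Yes, the clock has started | Visits, time, pathway |
| Never opened | No route stated | Promised, but no date | Absence of use only |

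All three groups have the Timepoint 1 interview. It precedes access, so it records anticipated barriers, not experienced ones.

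**Step 2. Timing.** The running text has the questionnaire follow directly on reaching the end of the site. Table 1, row 3, puts it with data collected 1–2 weeks after delivery of the training. The interview is also anchored in two ways: access in the text, delivery in the table. Row 2 of Table 1 is not in the text available to me, so this comparison rests on rows 1 and 3.

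**Step 3. The planned numbers.** With nine homes (Settings, participants and data collection): managers 9 × 1 = 9, staff 9 × 4 = 36, family members 9 × 6 = 54. These match the stated totals. Staff and family members together are 36 + 54 = 90, the population meant to complete the questionnaire.

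**Step 4. Size of the selection effect.** The document gives no completion or satisfaction rate, so the following are assumptions. Let c be the share who finish, p_f the share satisfied among finishers and p_n the share among non-finishers. All finishers are assumed to answer.

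- All-enrolled value = c × p_f + (1 − c) × p_n
- Overstatement = p_f − all-enrolled value = (1 − c) × (p_f − p_n)
- With nothing known about p_n, the all-enrolled value lies between c × p_f and c × p_f + (1 − c)

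With p_f = 0.90 and 90 participants:

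| c | Questionnaires | Overstatement, p_n = 0.90 | p_n = 0.60 | p_n = 0.30 | All-enrolled range, p_n unknown |
|---|---|---|---|---|---|
| 0.90 | 81 | 0 points | 3 points | 6 points | 81% to 91% |
| 0.70 | 63 | 0 points | 9 points | 18 points | 63% to 93% |
| 0.50 | 45 | 0 points | 15 points | 30 points | 45% to 95% |

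Example, c = 0.70 and p_n = 0.60: 0.30 × 0.30 = 0.09. The bounds are 0.70 × 0.90 = 0.63 and 0.63 + 0.30 = 0.93.

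The formula applies to items that a non-finisher could answer. Ratings of the website have no meaning for someone who never opened it.

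**The case against.** A reader might infer that drop-outs and non-users are lost to the evaluation and that acceptability as a whole is biased upward. The article does not support that.

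- Anyone who opened the site and stopped has accessed it, so the interview is due, and its themes include satisfaction and acceptability.
- Adoption rests on interviews as well as on quantitative indicators, so selection in the questionnaire does not carry over unchanged to the acceptability assessment.
- Baseline interviews ask about barriers before access, and analytics show partial use. Neither gives the reasons for stopping.
- Never-users fall within the promise to interview all participants. The fault is a missing date, not a stated exclusion.

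Further points have weight. Timing from access is sensible for users, because the Limitations section lets people use the resources when they choose; dating everything from the email would survey slow starters before exposure. The sample is purposive and the analysis descriptive, with no threshold or test to distort. Table 1 is a summary, and the timing mismatch may be loose wording.

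It can also be said that an article leaves the handling of non-starters to the full protocol. That answers less. The article does not merely omit a detail: it states a trigger and a clock, and followed as written these give the results in Step 1.

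**Conclusion.** The point holds in a limited form. The questionnaire data will describe finishers only, never-users have no defined interview date, and the text and Table 1 disagree on when the questionnaire is completed. These three statements rest on the wording and need no assumption.

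That the questionnaire results lean favourable is a plausible inference for that component, not an established result, and it should not be extended to acceptability overall. The 3 to 30 points depend entirely on assumed rates.

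No power, error rate or planned number is affected. In a descriptive case study this is a worthwhile, inexpensive improvement and not a must-fix.

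**What to change.** 1. Keep the end-of-website questionnaire for those who finish.
2. Set one cut-off after the access email. At that date, send a short version to every enrolled staff and family participant who has not finished. Ask how far they got and why they stopped or did not start. Put the user-experience items only to those who opened the site.
3. Keep interviews at 1–2 weeks after access for users. For non-users, date the interview from the cut-off.
4. Report questionnaire results beside the numbers enrolled, accessing and finishing, with finishers labelled as a subset.
5. Make Table 1 and the text give the same questionnaire timing and the same interview anchor.

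This is feasible because every participant is enrolled and contactable before access is given. The cost is one extra email, a few items and a wording change. Some non-finishers will not reply, so selection is reduced rather than removed, and the feedback may look less favourable.
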